### Sample size

Power calculations, based on the studies carried out by Brennan et al. [18] and Fritz et al. [12], were performed for the 3 main outcomes (for all: power 0.9; alpha 0.05). To detect a clinically relevant mean difference between the classification group and the usual care group of 9 points on the ODI (standard deviation [SD] 16), 55 patients are needed per group. To detect a clinically relevant mean difference of 2 points (SD 2) for pain (11-point numerical rating scale), 2 groups of 21 patients are needed. To detect a 20% difference in the dichotomised global perceived recovery (recovered vs. not recovered), 68 patients are needed per group. Anticipating a potential drop-out of 10%, 75 participants per treatment group (total n = 150) will be recruited.

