### Primary outcome measures

Global perceived recovery will be measured by self-assessment on a 7-point Likert scale ranging from "completely recovered" to "worse than ever" [30]. This will be dichotomised into success (complete and much recovered) and non-success (slightly recovered, no change, slightly worse, much worse and worse than ever). This measure has been found to be useful in LBP research [31].

Functional status will be measured according to the Dutch translation of the ODI, version 2.1a [32,33]. The ODI is sub-divided into 10 sections related to activities of daily living. Each section consists of 6 graded responses, scored 0-5, and the total score can range from 0 (no difficulty at all) to 50 (maximal difficulty). The ODI is widely used in LBP studies, and has also been used as a primary outcome measure in studies focusing on the treatment-based classification approach [12,18].

Pain intensity over the previous week will be measured on an 11-point numerical rating scale (0 = no pain to 10 = worst imaginable pain), with reliability, validity, and sensibility to change that are commonly accepted in LBP research [34-36].

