### Data-analysis

Baseline characteristics of the two intervention groups with regard to the most important prognostic indicators and main outcome measures will be compared to assess the adequacy of the randomisation. If necessary, adjustments will be made for baseline characteristics. The primary analysis will be an intention-to-treat analysis. A per protocol analysis will be performed to estimate the extent to which protocol deviations might have biased the results. The data will be analysed in a linear mixed model, with responses at 0 (baseline), 8, 26 and 52 weeks. In this model, the effect of interest is the time × treatment interaction. Estimates of treatment effects, with 95% confidence intervals between baseline and follow-up measurements, will be calculated and compared between the two treatment groups. Multivariable regression analysis will be used to adjust for possible baseline differences, and multilevel analysis will be performed, with PT, patient, and time of measurement as levels. Additionally, as a secondary analysis, a responder analysis will be performed according to the cut-off values as proposed by a consensus panel [50]. If there are many missing data, the missing data will be imputed with multiple imputation techniques.

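### The three sample sizes do not share one alpha, and the 68 per group for recovery that sets n = 150 gives 90% power only near the ends of the recovery-rate range

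*Protocol article*

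**What the plan says.** The Sample size section of the protocol article states that the calculations "were performed for the 3 main outcomes (for all: power 0.9; alpha 0.05"). It does not say whether alpha is one-sided or two-sided. Three sizes follow:

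- ODI: a difference of 9 points with an SD of "16), 55 patients are needed per group".
- Pain: a difference of 2 points with an SD of 2, giving 21 per group.
- Recovery: "To detect a 20% difference in the dichotomised global perceived recovery (recovered vs. not recovered), 68 patients are needed per group". The recovery rate expected under usual care is not given.

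Recovery needs the most patients, so it sets the total: "Anticipating a potential drop-out of 10%, 75 participants per treatment group (total n = 150) will be recruited".

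Under Primary outcome measures, recovery is defined from a 7-point scale: "This will be dichotomised into success (complete and much recovered) and non-success". The Data-analysis section plans "Estimates of treatment effects, with 95% confidence intervals between baseline and follow-up measurements".

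**The concern.** The ODI and pain calculations are printed with all their inputs, so they can be checked directly. If power and alpha are the same for all outcomes, one choice of sidedness should reproduce both.

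The recovery calculation cannot be checked in that way. The variance of a proportion depends on the rate, so a 20-point difference needs very different sizes at different usual-care rates. What can be checked is which rates make 68 correct.

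Recovery is a primary outcome and it determines n = 150. If 68 is right only at unusual rates, a null result on recovery could be reported as coming from a trial with 90% power when the real figure was well below that.

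**Working it through.** **Inputs.** Power 0.9 (z = 1.2816) and alpha 0.05 (z = 1.960 two-sided, 1.645 one-sided), ODI 9 points with SD 16, pain 2 points with SD 2, a recovery difference of 20% read as 20 percentage points, and 10% drop-out all come from the Sample size section. The usual-care recovery rate is not in the document. It is scanned here as an assumption.

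**1. ODI.** n per group = 2[(z_alpha + z_power) × SD/difference]².

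- Two-sided: 2[(1.960 + 1.2816) × 16/9]² = 66.4, so 67 (t-test: 68).
- One-sided: 2[(1.645 + 1.2816) × 16/9]² = 54.1, so 55 (t-test: 55).

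The printed 55 is reproduced one-sided only. With 55 per group, two-sided power is about 83% (t-test 83.2%, normal approximation 83.9%).

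**2. Pain.** The same formula with SD/difference = 1.

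- Two-sided: 2(1.960 + 1.2816)² = 21.01 (t-test: 23).
- One-sided: 2(1.645 + 1.2816)² = 17.1, so 18 (t-test: 18).

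The printed 21 matches the two-sided normal approximation, not the one-sided result. No single sidedness gives both 55 and 21.

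**3. Recovery.** Pooled two-proportion formula, with p̄ the mean of p1 and p2:

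n = [z_alpha √(2p̄(1−p̄)) + z_power √(p1(1−p1) + p2(1−p2))]² / (p2−p1)².

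Example, 40% versus 60%, two-sided: [1.960 × √0.50 + 1.2816 × √0.48]² / 0.04 = (1.386 + 0.888)² / 0.04 = 129.3, so 130.

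The power column uses the same formula solved for power. At 40% versus 60% with 67 per group: (0.2 × √67 − 1.386)/√0.48 = 0.36, which corresponds to 64%.

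| Usual care vs classification (assumed) | n per group, two-sided | n per group, one-sided | Two-sided power, 67 per group |
|---|---|---|---|
| 6% vs 26% or 74% vs 94% | 69 | 56 | about 89% |
| 10% vs 30% or 70% vs 90% | 82 | 67 | 83% |
| 20% vs 40% or 60% vs 80% | 109 | 89 | 72% |
| 30% vs 50% or 50% vs 70% | 124 | 101 | 66% |
| 40% vs 60% | 130 | 106 | 64% |

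The usual-care rate at which 68 per group gives exactly 90% power is 5.9% two-sided and 10.5% one-sided, or the mirror values near 74% and 69.5%. Below the lower value or above the upper one, fewer than 68 suffice. Unpooled, arcsine and continuity-corrected formulas move the two-sided rates only to about 3 to 7% or 73 to 77%.

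Between about 11% and 69%, 68 per group misses 90% under either sidedness. At 40% versus 60%, one-sided power with 68 is 76%.

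Solving the two-sided formula for the difference at 67 per group and 90% power gives about 23 to 27 points for usual-care rates of 10 to 50%.

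**4. Effect on the other outcomes.** After 10% drop-out, 75 × 0.9 = 67.5 per group remain. At 67 to 68 per group the ODI has about 90% two-sided power (t-test 89.8% at 67, 90.3% at 68). Pain needs at most 23 and is amply covered.

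**The case against.** **Sidedness is not stated.** One-sided 5% would explain both the 55 and the 68 (at about 10% versus 30% or 70% versus 90%) and leave only pain's 21 as the exception. A reader might infer that 68 is right only at about 6% or 74%, but that holds for a two-sided test alone. The 95% intervals in the Data-analysis section point to two-sided testing, though this is an inference about the analysis and not a statement about the sample size. The objection stands, so both sets of rates are given. It does not rescue the claim of one alpha for all three outcomes.

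**The usual-care rate is unknown.** A reader might infer that the trial is underpowered for recovery. The document does not support that as a fact. The calculations are said to rest on two earlier trials whose recovery rates are not shown, and nothing excludes a rate near either end of the range. An article may also leave such an assumption to the full protocol. What remains is that the 90% claim is printed without qualification and fails over most of the range.

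**The ODI slip changes nothing in practice.** This is correct. A reader might take the wrong ODI figure as the reason that recovery, or the total, falls short. It is not: recovery sets the total, and the total covers the ODI.

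**The drop-out step.** 68/0.9 = 75.6, while 75 × 0.9 = 67.5, which is half a patient below 68. This is too small to be a point in itself.

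**The formula is not the planned analysis.** The power figures describe a comparison of two proportions at one time point. The planned repeated-measures and multilevel models could have higher or lower power. This limits how literally the percentages should be read, but the section's own claim rests on the same kind of simple calculation.

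**Conclusion.** The point holds in two parts.

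First, the statement "for all: power 0.9; alpha 0.05" cannot be true of all three printed sizes under one sidedness. The ODI figure is one-sided and the pain figure two-sided. This follows from the document's own inputs and needs no assumption. It is a reporting error with no effect on the final size.

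Second, the recovery figure that sets n = 150 delivers 90% power only towards the ends of the range of usual-care rates. For rates between about 11% and 69% it does not, under either sidedness. The shortfall depends on the rate: with 67 evaluable per arm, two-sided power falls from 83% at 10% or 70% to 64 to 66% at 30 to 50%. At those middle rates, a true 20-point benefit would be missed about one time in three.

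These percentages rest on assumed rates, on reading 20% as percentage points, and on a single-time comparison of two proportions. Reading 20% as a relative difference makes the shortfall larger: even 80% versus 96% needs 85 per group two-sided.

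**What to change.** Keep n = 150 and rewrite the sample-size paragraph:

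- State two-sided alpha 0.05 for all three outcomes.
- Correct the ODI requirement to 67 to 68 per group, and note that it is still met, with about 90% power, at 67 to 68 evaluable per group.
- For recovery, state the assumed usual-care rate and its source, with the actual power at about 67 evaluable per group. Alternatively, give the difference detectable with 90% power, which is about 23 to 27 points for usual-care rates of 10 to 50%.
- Remove the claim of 90% power for all outcomes unless the assumed recovery rate supports it.

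The cost is rewording, with no extra patients. The stated power for recovery may become less favourable. The rewording discloses any shortfall but does not remove it, and a null result on recovery should then be read against the restated power.

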### Data-analysis

Baseline characteristics of the two intervention groups with regard to the most important prognostic indicators and main outcome measures will be compared to assess the adequacy of the randomisation. If necessary, adjustments will be made for baseline characteristics. The primary analysis will be an intention-to-treat analysis. A per protocol analysis will be performed to estimate the extent to which protocol deviations might have biased the results. The data will be analysed in a linear mixed model, with responses at 0 (baseline), 8, 26 and 52 weeks. In this model, the effect of interest is the time × treatment interaction. Estimates of treatment effects, with 95% confidence intervals between baseline and follow-up measurements, will be calculated and compared between the two treatment groups. Multivariable regression analysis will be used to adjust for possible baseline differences, and multilevel analysis will be performed, with PT, patient, and time of measurement as levels. Additionally, as a secondary analysis, a responder analysis will be performed according to the cut-off values as proposed by a consensus panel [50]. If there are many missing data, the missing data will be imputed with multiple imputation techniques.

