
### Treatment allocation

To conceal the treatment allocation, an independent researcher who is not involved in the selection of the patients will randomise each patient to one of the two treatment groups. Randomisation lists will be generated by computer before the study starts, pre-stratified for the duration of the complaints (6-12 weeks or >12 weeks) and disability (Oswestry Disability Index [ODI] <25% or ≥25%) to prevent unequal distribution. To prevent unequal treatment-group sizes, the patients will be randomised according to a stratified block randomisation method, in blocks of four. No treatment will be given prior to randomisation.

Directly after the randomisation procedure, the PT who will provide treatment will be informed about the group allocation. Patients will be scheduled for their first treatment session as soon as possible in the private practice they attended.

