### Physical therapists in the participating clinics

All patients will be treated by PTs in the participating clinics. In each clinic, at least one PT will be instructed about the classification system, and at least one PT will be instructed about the usual care procedure, depending on preference and expertise. PTs who will provide manipulation treatment must be licensed, post-graduate MTs or in the 4^th ^and final year of the MT master education program at the Educational Center for Musculoskeletal Therapies (SOMT) in the Netherlands. No extra qualifications will be required to treat patients according to the classifications of direction-specific exercises and stabilisation. The number of years of experience of the PTs, and their post-graduate education in MT and/or MDT, will be recorded for both treatment groups. To minimise contamination, the PTs who will provide the classification-based treatment will not be allowed to provide usual care, and vice versa.

The PTs who will provide the classification-based treatment will follow a five-hour training session in which the treatment protocols will be described and discussed. Experts on direction-specific exercises ([name]) and stabilisation will provide the training. The PTs will receive a detailed manual of the study, and a translation of the registration forms and treatment protocols used in the Brennan et al. study [18]. The PTs providing usual care will receive a two-hour training course in the rationale and treatment components described in the LBP guidelines issued by the Royal Dutch College for Physical Therapy (KNGF) [27,28].

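### For ODI and pain, a therapist level entered as an ordinary random intercept cancels from the time × treatment contrast when week 0 is a response, so that contrast is not adjusted for therapist

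*Protocol article*

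**What the plan says.** All references are to the protocol article; no statistical analysis plan is at hand.

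- **Data-analysis**, model: "The data will be analysed in a linear mixed model, with responses at 0 (baseline), 8, 26 and 52 weeks".
- **Data-analysis**, target: "In this model, the effect of interest is the time × treatment interaction".
- **Data-analysis**, after a clause on adjusting for baseline differences by regression: "multilevel analysis will be performed, with PT, patient, and time of measurement as levels". The section does not say whether PT and patient effects are intercepts only or may vary over time, and it names no residual covariance.
- **Treatment allocation**: "No treatment will be given prior to randomisation".
- **Physical therapists in the participating clinics**: "the PTs who will provide the classification-based treatment will not be allowed to provide usual care, and vice versa". Each clinic is to have at least one PT for each arm.
- **Sample size**: "for all: power 0.9; alpha 0.05", with no allowance for clustering and no ICC or caseload.
- **Table 1**: ODI and pain are measured at weeks 0, 8, 26 and 52. Global perceived recovery is measured at weeks 8, 26 and 52 only.

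**The concern.** A PT can affect a trial patient's outcome only after treatment starts, and each PT works in one arm. PT differences therefore enter the between-arm comparison of change. The article expects such differences: its sections on usual care and on the contrast between interventions describe techniques and strategies that vary between PTs. Naming PT as a level suggests that the authors meant to allow for this.

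A random intercept for PT, however, adds the same amount to all four measurements of that PT's patients, week 0 included. The interaction is a contrast of change, so the constant drops out. The fitted model could then contain a PT term while the interval for the effect of interest is the same as without it. A few unusually good or poor PTs in one arm could be read as an effect of classification-based care on ODI or pain, with the interval presented as allowing for therapist.

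**Working it through.** **Step 1: cancellation.** For patient i of PT k at visit t, with random intercepts only:

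y(ikt) = mean(t) + effect(t) × arm + u(k) + v(i) + e(ikt).

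Subtracting week 0 gives

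y(ikt) − y(ik0) = [mean(t) − mean(0)] + [effect(t) − effect(0)] × arm + e(ikt) − e(ik0).

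Both u(k) and v(i) are gone. REML fits to simulated complete data confirm it. In one data set the standard error of the interaction was 2.560494 with the patient level only and 2.560494 with PT and patient levels. In another it was 2.7009 both ways.

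**Step 2: size from PT effects alone.** Inputs from the article: alpha 0.05, taken as two-sided to match the 95% intervals; 75 per arm, or 68 per arm after drop-out; SD 16 for ODI, which only sets the scale. Assumed, because the article gives neither: m patients per PT, equal across PTs, and ICC, the share of the variance of change that lies between PTs.

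The true variance of the contrast exceeds the credited one by about 1 + (m − 1) × ICC, so

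type I error = 2 × [1 − Φ(1.96 / √(1 + (m − 1) × ICC))].

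- ICC 0: 2 × [1 − Φ(1.96)] = 5.0%, the plan's own figure. Simulation gives 4.8–5.5%.
- m = 3, ICC 0.05: ratio 1.10, error 6.2%.
- m = 3, ICC 0.10: ratio 1.20, 1.96/1.095 = 1.789, error 7.4%.
- m = 5, ICC 0.10: ratio 1.40, 1.96/1.183 = 1.656, error 9.8%.
- m = 10, ICC 0.10: ratio 1.90, 1.96/1.378 = 1.422, error 15.5%.

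Simulation of the week-52 contrast with equal correlations agrees:

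- 68 per arm, 6,000 trials per setting: 6.6% (m = 3, ICC 0.05), 10.5% (m = 5, ICC 0.10) and 15.4% (m = 10, ICC 0.10).
- 75 per arm, about 4,000 trials per setting: 6.8% (m = 3, ICC 0.05), 7.9% (m = 3, ICC 0.10), 10.2% (m = 5, ICC 0.10) and 15.9% (m = 10.7, ICC 0.10).

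Reaching 10% needs (m − 1) × ICC = (1.96/1.645)² − 1 = 0.42. That is about 5.2 patients per PT at ICC 0.10, or 9.4 at ICC 0.05.

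**Step 3: variance shared by clinic.** Suppose half of a total ICC of 0.10 is at clinic level, each clinic has one PT per arm, and m = 10. The clinic part cancels between arms, leaving a ratio of 0.90 + 10 × 0.05 = 1.40 and an error of about 9.8% instead of 15.5%.

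**Step 4: a separate effect of equal correlations.** Intercepts with independent residuals imply one correlation for all pairs of visits. Assume 0.4 between baseline and each follow-up, and 0.7 between follow-ups. The average over the six pairs is (3 × 0.4 + 3 × 0.7)/6 = 0.55. In units of the outcome variance, the credited variance of change is 2 × (1 − 0.55) = 0.90, and the true one is 2 × (1 − 0.4) = 1.20. The ratio is 1.333, and 1.96/√1.333 = 1.697 gives an error of about 9.0%. Simulation gives 9.3% with no PT effect at all.

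**Step 5: does the remedy work?** With week 0 as covariate, a PT random intercept at week 52 and t on (number of PTs − 2) degrees of freedom, 1,000 trials per setting at correlations 0.4/0.7 rejected in 4.9% (14 PTs per arm, ICC 0.10) and 5.0% (23 PTs per arm, ICC 0.05). The intercept-only model rejected in 15.9% and 10.6% of trials in the same settings.

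**The case against.** The strongest reply is that the article names levels and no more. It does not say intercepts only, and PT effects that vary over time fit its wording. The form of the random effects, the residual covariance and the degrees of freedom are details that an article may leave to a fuller document. The multilevel clause also stands in a later sentence than the model with week 0 as a response, beside the clause on baseline adjustment. Read together with that clause, the PT intercept would act on follow-up, which is close to the remedy below. All of this stands. The defect is conditional on the plain reading and is not shown to be the intended model.

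A reader might infer that the type I error will be two to four times 5% because of the therapist term. The documents do not support that. Caseload, ICC and correlations are all assumed. Ten patients per PT means about 7 PTs per arm (68/10), while up to 300 clinics are to be invited, so small caseloads are quite possible. Values near 20% appear only when the correlation misfit of step 4 is added to PT effects (20.4% at 10 per PT, ICC 0.10), or with very few PTs. Clinic-level variance shared by both arms lowers the excess further.

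What remains is that an analyst who follows the section literally could fit a model whose PT level does nothing for the effect of interest. Ruling that out takes a sentence or two.

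**Conclusion.** The point holds in conditional form, for ODI and pain only. With week 0 as a response, time × treatment as the target and random intercepts for PT and patient, the PT term cancels exactly with complete data. PT differences arising after baseline are then not in the standard error.

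- **Size from PT effects alone** (equal correlations, equal caseloads, about 68–75 per arm): about 5–7% at 1–3 patients per PT with ICC up to 0.10 (7.9% in simulation at the top of that range), about 10% at 5 per PT and ICC 0.10, and about 15–16% at 10 per PT and ICC 0.10. It is less where clinics account for part of the variance.
- **Separate correlation problem**: about 9% with no PT effect, under the assumed 0.4/0.7 pattern and independent residuals.

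No single multiple of the nominal level can be stated. The conclusion should not be carried over to global perceived recovery, since a model with a baseline response cannot apply to an outcome without a baseline value. This is a worthwhile and inexpensive improvement; it does not show that the planned analysis is invalid.

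**What to change.** For ODI and pain, state the intention-to-treat model as follows:

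- responses at weeks 8, 26 and 52, with week 0 as covariate;
- a PT random intercept, which now acts on follow-up only;
- an unstructured within-patient covariance in place of a patient intercept alone;
- small-sample degrees of freedom that reflect the number of PTs (for example Kenward-Roger);
- the treatment difference at each follow-up as the effect of interest. In this form the interaction would only compare follow-ups with each other, and a constant PT effect would cancel from it again.

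Alternatively, keep week 0 as a response and the interaction as target, and add a PT × post-baseline random effect (zero at week 0) to any constant PT or clinic term. Keeping the constant term matters, because clinic case-mix may cluster the baseline scores. If PT effects varying over time were intended all along, one clause saying so settles the main point. Report the number of PTs, the patients per PT and the estimated PT variance.

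The cost is one or two sentences and no new data, since the treating PT is known. Intervals become somewhat wider where therapists differ: in one simulated data set (10 PTs per arm, ICC 0.10) the standard error rose from 2.70 to 2.96, about 10% (2.96/2.70 = 1.10). A few more covariance parameters have to be estimated.
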